**Figure 1 figure1:**
[figure not shown]
Diagrammatic flow in terms of sequence of events on the Acceset digital text-based intervention (ie, the platform). CSQ-8: Client Satisfaction Questionnaire-8; GAD-7: Generalized Anxiety Disorder-7; MPSS: Multidimensional Scale of Perceived Social Support; PHQ-9: 9-item Patient Health Questionnaire; RMS: Rosenberg Mattering Scale.

### Ethics Approval

This study will be performed in line with the principles of the Declaration of Helsinki. Approval was granted by the Ethics Committee of the NUS (protocol S-20-144). Informed consent will be obtained from all individual participants included in the study.

### Eligibility Criteria

The seeker inclusion criteria are as follows: emerging adults aged 19 to 25 years who are distressed but healthy—specifically, these individuals should exhibit some symptoms but have not been formally diagnosed with depression, anxiety, or a mental health disorder. The exclusion criteria (seekers) will include emerging adults who, during screening, are deemed to be at a high risk of suicide using a validated and standardized psychological scale (PHQ-9) [37,38]. On the basis of empirical studies, the proposed cutoff is PHQ-9 >9, which has a sensitivity of 88% and specificity of 88% for major depression [37]. Above a score of 9, seekers will not be recruited for the study, and they will be referred or directed to different clinical mental health support providers, including counseling centers and hotlines, on the NUS campus.

The rationale for including individuals who do not meet the criteria for depression is that the Acceset intervention focuses on befrienders as peer supporters to seekers, and these befrienders are not certified and accredited counselors, unlike moderators. Importantly, it is not the responsibility of the befriender to serve as an advisor, solve the seekers’ problems, or provide diagnoses of potential mental health issues. Inclusion of individuals who meet the criteria for depression would require support from professional counselors who have formal trainings and certifications. However, Acceset as an intervention platform is designed primarily for a healthy population of young people without formal diagnoses of mental health conditions to provide peer support.

The inclusion eligibility criteria also apply to befrienders, with an additional criterion of being aged ≥21 years. Seeker exclusion criteria apply to both befrienders and moderators. Moderator inclusion criteria are as follows: adults aged ≥21 years with certified trainings and accreditations (ie, at least a master’s degree in social sciences or Counseling that is recognized by the Ministry of Education, Singapore, and the Executive Counselling and Training Academy) and professional experiences in providing counseling services to emerging adults. The exclusion criteria apply to both seekers and befrienders.

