The moderation protocol at the participant recruitment stage entails the screening of seekers using a validated psychological scale—the 9-item Patient Health Questionnaire (PHQ-9)—to exclude individuals at high risk of depression and suicidality. During the intervention phase, befrienders are also trained to alert moderators when seekers are at an unacceptably high risk of depression and suicidality, and the moderator vets all the letter exchanges between the seekers and befrienders for content of high negativity and suicidal thoughts and expressions. This moderation protocol aims to identify seekers who are at an unacceptably high risk of depression and suicidality and refer them to an appropriate mental health care provider, including counseling centers and hotlines, on the NUS campus.

Each befriender will provide support to 3 seekers, receive notification from the Acceset platform on incoming letters, and work in partnership with the moderators to address the seekers’ issues during the 3 weeks of letter exchange. Befrienders have the choice to discontinue the letter exchange with seekers if they feel discomfort having to address issues that they find challenging by informing trained moderators. Given the sensitive nature of the letter content, there may be issues that befrienders will be exposed to that they are not fully comfortable with and may cause distress. Therefore, it is a deliberate design to ensure that the befrienders are not left on their own in handling cases and that they work in partnership with the 2 trained and certified moderators to address the seekers’ issues. The first point of contact for the befriender will be the 2 trained and certified moderators. In such cases, the befriender’s workload decreases to 2 seekers.

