With regard to user referral to appropriate mental health support providers, the seeker-befriender-moderator interaction will identify participants at an unacceptably high risk of depression and suicidality before and during engagement based on 3 means. First, the Acceset algorithm will scan the content of the letter exchanges for high negativity and suicidal thoughts and expressions. Second, moderators with the required background and assessment tools will identify seekers at risk by vetting all the letter exchanges for high negativity and suicidal thoughts and expressions. Third, seekers will self-report their responses to the PHQ-9, and those that meet the clinical cutoff scores (PHQ-9 >9) will be excluded at the start of the study. During the course of the study across the 4 time points, seekers with an unacceptably high risk of depression and suicidality (PHQ-9 >9) will be referred to an appropriate mental health care provider, including counseling centers and hotlines, on the NUS campus. Seekers’ self-reported responses to the PHQ-9 serve as the primary risk assessment to make referrals to appropriate mental health support providers.

At recruitment, we will assess the percentage of participants identified as being at an unacceptably high risk of depression and suicidality meeting the clinical cutoff of PHQ-9 >9 that has a sensitivity of 88% and specificity of 88% for major depression [38] and exclude them from the study. During the course of the study, we will ascertain the percentage of events when a befriender correctly alerts the moderator that the seeker is at an unacceptably high risk of depression and suicidality as confirmed by the moderator, who will vet every letter exchange. During the course of the study and for every letter exchange, we will tabulate the percentage of events when a moderator correctly identifies a seeker with an unacceptably high risk of depression and suicidality. Both the befrienders and moderators will use the PHQ-9 as a systematized coding structure to code seekers’ letter content to ensure generalizability and validity in risk assessment across both coders—befrienders and moderators. Finally, we will tabulate the percentage of events when a seeker who is at an unacceptably high risk of depression and suicidality (both during the recruitment process and during engagement with the platform) receives directions to an appropriate mental health care provider, including counseling centers and hotlines, on the NUS campus.

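### The seeker exclusion is stated as high suicide risk and reported as combined depression and suicidality risk, but the rule applied is a PHQ-9 total above 9 that the article supports only for major depression

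*Protocol article*

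**What the plan says.** Four places in the protocol article's Methods bear on this.

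- **Eligibility Criteria, first paragraph.** Seekers are excluded if "deemed to be at a high risk of suicide using a validated and standardized psychological scale (PHQ-9". The text continues that "the proposed cutoff is PHQ-9 >9, which has a sensitivity of 88% and specificity of 88% for major depression", and that "Above a score of 9, seekers will not be recruited for the study".
- **Eligibility Criteria, second paragraph.** The reason given for leaving these people out is that befrienders are not accredited counselors, and that people who meet criteria for depression would need professional support. Suicide is not mentioned.
- **Participants and Study Setting.** The PHQ-9 screen at recruitment is there "to exclude individuals at high risk of depression and suicidality".
- **Implementation Outcomes.** At recruitment, "we will assess the percentage of participants identified as being at an unacceptably high risk of depression and suicidality", defined by the "clinical cutoff of PHQ-9 >9 that has a sensitivity of 88% and specificity of 88% for major depression". During the study, "seekers with an unacceptably high risk of depression and suicidality (PHQ-9 >9) will be referred to an appropriate mental health care provider". The section makes the PHQ-9 self-report the primary assessment for referral. It adds that the participant information sheet uses the same cutoff, under the same combined label, as the condition for sharing a seeker's information with the campus counseling center.

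Clinical Outcomes names the PHQ-9 as the measure of depression.

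**The concern.** One number, a PHQ-9 total above 9, carries three names: high suicide risk, combined depression and suicidality risk, and a screen for major depression. Evidence is offered only for the last.

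This matters because the total is also a reported result. Hypothesis 1c holds that the platform is feasible and acceptable partly because it identifies people at high risk related to depression and suicidality, and the percentage above the cutoff at recruitment is one of its outputs. If the plan is followed as written, a count of positive depression screens is published under a label that includes suicidality. A reader could take it for the share of applicants at high suicide risk, or take the admitted group to have been screened for suicide risk with known accuracy. The article supports neither reading.

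**Working it through.** The point rests on setting the statements side by side. The 88%/88% figure comes from cited work and no counts are given, so it cannot be reproduced here.

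**Step 1. What each place names, and what supports it.**

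| Place | Condition named | Rule | Support stated |
|---|---|---|---|
| Eligibility Criteria, exclusion sentence | Suicide alone | PHQ-9 above 9 | 88%/88%, major depression |
| Eligibility Criteria, rationale | Depression | Same | Befrienders are not professional counselors |
| Participants and Study Setting | Depression and suicidality | PHQ-9, no cutoff given there | None given there |
| Implementation Outcomes, at recruitment | Depression and suicidality | PHQ-9 above 9 | 88%/88%, major depression |
| Implementation Outcomes, referral and information sheet | Depression and suicidality | PHQ-9 above 9 | None given there |
| Clinical Outcomes | Depression | PHQ-9 as outcome scale | Citation |

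Both statements of accuracy name major depression. Only one sentence names suicide alone.

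**Step 2. Is there a separate suicide rule?** The exclusion is triggered by the total score. The text shown states no item-level rule and no accuracy for suicide risk.

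**Step 3. Does accuracy for major depression carry over to suicide risk?** Not without further information. As an illustration, assume that PHQ-9 positivity depends only on whether a person has major depression, and let q be the share of people at suicide risk who have it. Then

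implied sensitivity for suicide risk = q × 0.88 + (1 − q) × (1 − 0.88).

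- q = 0: 0.12
- q = 0.25: 0.22 + 0.09 = 0.31
- q = 0.50: 0.44 + 0.06 = 0.50
- q = 0.75: 0.66 + 0.03 = 0.69
- q = 1: 0.88

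Under that assumption, 88% carries over only if everyone at suicide risk has major depression. The article gives no q and the assumption is untested, so the range shows why the figure cannot be borrowed. It does not estimate the screen's real accuracy or the size of the defect.

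**Step 4. Where it enters the results.** The recruitment percentage under hypothesis 1c is defined by the cutoff. The befriender-alert and moderator-identification percentages come from letters but carry the same combined label, and both groups code letters with the PHQ-9. As described, those figures do not separate suicidal content from depression either.

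**The case against.** Much of the opposing case is right.

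- **The article never claims 88%/88% for suicidality.** This stands. A reader might infer such a claim from the exclusion sentence and the accuracy sentence standing next to each other, but both times the figure is tied expressly to major depression.
- **Suicide alone is named once.** This stands. Elsewhere the label is combined, and the quoted accuracy supports its depression half.
- **Hypothesis 1c has other legs.** This stands. It names three means, and two of them, the letter algorithm and moderator vetting, look directly for suicidal content. A reader might infer that the safety claim rests on the cutoff alone; the text does not say that. Those two means work on letters, however, so they cannot support the recruitment screen, which comes before any letter.
- **The label is defined openly.** This stands in part. The cutoff is printed beside the label in Implementation Outcomes, so a careful reader can see what is counted. The name still says more than the count shows.
- **A condensed article need not carry validation data, and the cited sources and the questionnaire appendix are not at hand.** This stands as far as it goes: support for the cutoff as a suicide screen may exist there. It does not remove the point, which is that a stated purpose, a stated rule and a stated reported outcome do not match one another.

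**Conclusion.** The point holds as an inconsistency of purpose, rule and label. The exclusion is described as one for high suicide risk, the rule and rationale are about depression, and the resulting count is to be reported as combined depression and suicidality risk. The recruitment percentage can be read as a percentage with a positive depression screen. It cannot be read as a percentage at high suicide risk.

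No size can be computed for the suicidality half. Predictive values for major depression at assumed prevalences would not measure it, because accuracy for major depression is not what is in question. Nor can one infer that the cutoff fails to detect suicide risk: the property is not shown here, which is different from being shown to be absent.

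The consequence is limited to the eligibility wording, the referral label, the information sheet and the hypothesis 1c results. The between-arm comparison, the sample size and the significance level are not affected. The conclusion depends on the article's text alone and on no assumed figure.

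**What to change.** 1. Reconcile the stated purpose and the rule in Eligibility Criteria with each other, and then with Participants and Study Setting and with Implementation Outcomes, including its account of the information sheet. Which clinical rule applies is for the sponsor to settle.
2. In the hypothesis 1c results, report the percentage with PHQ-9 above 9 as a positive depression screen.
3. Tabulate flags for suicidal content from the letter algorithm, befrienders and moderators separately from depression flags. The algorithm and moderators already look for such content, so this is workable.

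The Results section says data collection is complete and analysis is in progress. The screen has therefore been applied, but labels and tables can still be corrected. The cost is some rewording and one extra table row. The risk-identification claim becomes slightly less favourable, because the PHQ-9 count no longer stands for suicidality.

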### The Intervention

The Acceset intervention for this preliminary study comprises (1) training for befrienders to apply mattering, selfhood, compassion, and mindfulness to provide effective digital peer support (refer to the digital peer support training curriculum in Multimedia Appendix 4) and (2) a text-based intervention with Acceset incorporating digital markers that assess the following outputs: psychological well-being and the degree of community engagement as well as peer emotional disclosure [37].

### Digital Peer Support Training

The core objective of Acceset is to enable peer befrienders to effectively support peer seekers. Befrienders will receive 4 hours of web-based training conducted by a licensed clinical or educational psychologist. This training consists of 1 hour of instructional content that enhances the befriender’s knowledge of mattering, selfhood, compassion, and mindfulness and 2 hours of workshop training on the practical skills of applying these components to provide effective peer support.

Selfhood refers to self-knowledge (an awareness of one’s strengths and unique qualities) [41]. The second type of selfhood is the interpersonal self (how the self evolves based on our interactions and relationships with others). The interpersonal self creates and sustains relationships and fulfills important roles to keep a favored position in the social system. The third type of selfhood refers to the self as an agent (having agency, control, and persistence in achieving a goal despite failure, frustration, and discouragement). Mattering, which refers to the extent to which we are important to the world and people around us [42], consists of three components: (1) importance (the interest and concern others bestow on us), (2) attention (from others; the extent to which people are aware of our presence and unique qualities), and (3) reliance (the degree to which others turn to us and make us feel that we are needed).

Compassion comprises 3 theoretical orientations—having compassion for others, receiving compassion from others, and having self-compassion—in reducing psychological distress and symptomologies [43], and there are 3 stages of developing compassion based on the well-established Compassion Cultivation Training with evidence from accumulating RCTs [44]. In the first stage, individuals become aware of their distress and develop self-compassion; in the second stage, they develop affective concern; and, in the third stage, they gain personal insights into the wish and readiness to relieve one’s distress [44]. Mindfulness will be regarded as a flexible cognitive state in which individuals are actively present and notice novel aspects in both the environment and one’s perspectives [45].

The proficiency of befrienders in applying these digital support skills will be evaluated through simulation and homework activities in which they will apply these skills to simulated letters that are adapted from actual cases of peer seeker emotional disclosure on the Acceset platform. All assignments will be reviewed and given feedback on. At the end of the training, befrienders are expected to apply the 4 components to their assigned peers’ disclosed emotional experiences. All participants who complete the training will receive a training certificate and will be invited to take on live cases and be part of the study.

### Acceset Text-Based Intervention (the Platform)

Acceset aims to serve as an intervention to strengthen emerging adult mental well-being via 3 means—assessing their psychological well-being with 3 digital features: emotionality, motivations, and functional adjustment. These features are intended to support users with a peer emotional disclosure process while also engaging an interconnected and accessible Singapore ecosystem and community as the basis of the support system.

#### Digital Features

Participants’ emotionality, as reflecting their mental well-being, is assessed by their use of emotion stamps—a digital feature of the Acceset platform to measure negativity and positivity that is based on the Positive and Negative Affect Scale [46]. A total of 9 motivation graphic interface formats (GIFs)—dynamic images with corresponding captions—function to express a seeker’s motivation to engage with the Acceset platform. There are 3 innate psychological motivations [34]. These include competence (to exert control, cope with specific problems, and make changes to one’s behavior and environment), autonomy (to act from choice), and relatedness (the need to belong and connect with others). Acceset also has a set of functional adjustment stickers as indicators of internalized and externalized problems. Internalized problems refer to those directed inward—toward the self—and often manifest as “tension, unease, and distress” [47]. When these internalized symptoms compound, individuals may experience depression, anxiety, social isolation, and other challenges. On the contrary, externalizing problems are directed externally [48]. Individuals often disregard social norms and engage in conflicts and behaviors that cause discomfort to other people. When these externalizing problems are grouped together, they can potentially manifest as aggression, rule breaking, delinquency, and other behaviors.

#### Peer Emotional Disclosure

The Acceset text-based disclosure process collectively leverages technology and community engagement to form a web-based safety net for the development of a platform function that drives sustainable user engagement. This process begins when seekers engage with the Acceset platform to seek support with managing their emotional experiences. Before writing their first letter, seekers will select the social contexts of the issue. These may include friends, finances, family, work, and school. On the basis of the disclosed emotional experiences, the information presented will pertain to where the issues arise, with whom the issues occur, and which issues adversely affect mental well-being. During the course of the letter exchange, seekers will express their negativity and positivity through the emotion stamps, indicate their psychological needs using the motivation GIFs, and describe the effects of the emotional experiences through the function adjustment stamps.

The seeker-befriender interaction dynamic is facilitated digitally, with no in-person visits or interactions. Before and during the letter-writing process, a pop-up message reminds both befrienders and seekers that the use of the Acceset platform is to remain completely anonymous and that personal information may not be revealed in any way. In matching befrienders and seekers, 3 factors are considered: the timing when seekers reach out, the availability of befrienders, and befrienders’ knowledge of the nature of the seekers’ emotional experiences. Some befrienders may have more in-depth knowledge of certain issues based on their lived experiences and will prefer to support seekers on those issues. Thus, when the seekers write a letter, the social context of the letter is made known to the befriender, who will then select their preferred seeker based on their ability to relate and respond. The approach of matching befrienders and seekers is intended to facilitate effective peer support intervention [29]. Through the digital peer support training and the guidance of the moderators—certified counselors who will vet the e-letter drafts from the befrienders—the befriender’s role is to provide support by enhancing a sense of mattering, strengthening selfhood, exploring compassion, and cultivating mindfulness among seekers. Importantly, it is not the responsibility of the befriender to serve as an advisor, solve the seekers’ problems, or provide diagnoses of potential mental health issues.

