**Aims and hypotheses**
Aim 1: the first aim is to evaluate the implementation effectiveness of digital peer support training between emerging adults providing support (befrienders) and emerging adults seeking help (seekers).Research question 1a: is Acceset digital peer support training an effective training curriculum in providing peer support?Hypothesis 1a: the digital peer support training is effective for befrienders in providing peer support, as demonstrated by the adoption of and fidelity to the training curriculum.Research question 1b: is the Acceset text-based intervention (ie, the platform) feasible and acceptable (ie, safe and timely) as an ongoing mechanism of support for seekers and befrienders?Hypothesis 1b: digital peer support is feasible and acceptable in offering support for emerging adults’ mental well-being, which is evidenced by 2 indicators:The engagement of the seeker-befriender-moderator interaction across the 4 time points—baseline (before the intervention), 3 weeks (conclusion of the intervention), and 6 and 9 weeks (carryover effect assessment)—that is indexed by the waiting period for seekers to receive a response. Delays are defined as a >48-hour waiting period and will be categorized based on the following reasons: (1) technical factors (eg, the befriender is not able to log into the platform to respond in time) and (2) human factors (eg, the befriender drops out from the study, and no replacement is found in time). An acceptable response time is within 48 hours, and this is emphasized during Acceset digital peer support training for befrienders [37].The use of technical features of the Acceset platform that is measured by the seeker dropout rate at each stage of engagement with the Acceset platform, the number of visits on the study registration website, the number of participants who registered with Acceset, the average number of letters exchanged, and the average number of emotion and functional adjustment stickers and motivation graphic interface formats used [37].Research question 1c: is the Acceset text-based intervention (ie, the platform) feasible and acceptable (ie, safe and timely) as an ongoing mechanism of support that identifies individuals who are at an unacceptably high risk of mental health conditions?Hypothesis 1c: digital peer support is feasible and acceptable in offering support for emerging adults’ mental well-being by identifying individuals who are at an unacceptably high risk of mental health conditions related to depression and suicidality, which is measured before and during engagement based on 3 means—specifically, the Acceset algorithm detection of the content of the letters, the moderators’ vetting of the content of seekers’ letters, and the seekers’ self-report responses to the 9-item Patient Health Questionnaire [38] (refer to the Implementation Outcomes section for details [37]).Aim 2: the second aim is to elucidate whether Acceset digital peer support harnesses the 4 components of emerging adult mental health—mattering, selfhood, compassion, and mindfulness.Research question 2a: does Acceset digital peer support enhance the 4 components among seekers and befrienders?Hypothesis 2a: Acceset digital peer support (training) increases the 4 components among befrienders (before and after training) and seekers (over the course of the study across 4 time points).Research question 2b: is Acceset digital peer support effective in improving emerging adult mental well-being?Hypothesis 2b: digital peer support leads to significantly better mental well-being of seekers compared with the control group. This effect is sustained beyond the period of the intervention.Aim 3: the third aim is to investigate the mechanism of change in emerging adult mental well-being involving digital peer support (delivered by the Acceset platform).Research question 3: what is the mechanism explaining the change in emerging adult mental well-being involving digital peer support?Hypothesis 3: the initial level and rate of change (ie, growth factors) of befrienders’ web-based support positively predict the growth factors of seekers’ psychological well-being in accordance with latent growth curve modeling.

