The system will inform the seeker and obtain their consent to continue the conversation with a new befriender or end the letter thread. If the seeker chooses to continue, the system will notify all befrienders of the availability of an ongoing case, and interested befrienders can take it up. In addition, other trained befrienders (whom Acceset has trained beyond the recruited 30 befrienders for this study) will be activated to take up the case if no existing befrienders take it up. Similarly, when befrienders drop out of the study during the 3 weeks of letter exchanges, they will be replaced with other trained befrienders. Befrienders’, seekers’, and moderators’ use of the Acceset platform is to remain completely anonymous such that the 3 parties do not have direct contact with one another, and seekers do not have discretion to switch befrienders on their own. In the event of disagreement between seekers and befrienders (eg, seekers are concerned with how their issues are not adequately addressed during the letter exchange), they will be able to notify the study team. The system will inform the seeker and obtain their consent to continue the conversation with a new befriender or end the letter thread. If the seeker chooses to continue, the system will notify all befrienders of the availability of an ongoing case, and interested befrienders can take it up. However, it should be noted that such situations will be rare given that moderators will vet all letter exchanges and work in partnership with befrienders to ensure that their responses are satisfactory. If seekers drop out of the study, their befrienders will continue with the reduced workload.

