#### Mechanism of Action

For research question 3 and hypothesis 3, we will elucidate the mechanism of change that links digital peer support intervention to emerging adult mental well-being (Figure 3). Specifically, we will assess whether and how the level at the start of the study and the rates of change from baseline to weeks 3, 6, and 9 in befrienders’ support relate to seekers’ mental well-being.

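### Hypothesis 3 counts a path to the seeker's pre-intervention level as mechanism, and its path to the rate of change rests on pairs formed by befriender choice

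*Protocol article*

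**What the plan says.** **Pairing.** The section Peer Emotional Disclosure says that timing, availability and the befriender's knowledge of the issue all enter the match. When a seeker writes, "the social context of the letter is made known to the befriender". The choice of pair rests with that person, "who will then select their preferred seeker based on their ability to relate and respond".

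**Changes of befriender.** Participants and Study Setting states: "Befrienders have the choice to discontinue the letter exchange with seekers if they feel discomfort having to address issues that they find challenging". If the seeker agrees to go on, "the system will notify all befrienders of the availability of an ongoing case, and interested befrienders can take it up". Failing that, "other trained befrienders (whom Acceset has trained beyond the recruited 30 befrienders for this study) will be activated to take up the case". The seeker may instead end the thread.

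**Criterion.** Hypothesis 3 in Textbox 1, repeated under Principal Findings, is that "the initial level and rate of change (ie, growth factors) of befrienders’ web-based support positively predict the growth factors of seekers’ psychological well-being". The parenthesis defines growth factors as initial level and rate of change.

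**Timing.** The first of the four questionnaires is completed before the intervention. The others follow at weeks 3, 6 and 9.

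**Interpretation.** The latent growth curve paragraph of Data Collection, Management, and Analyses says that the model shows whether and how the intervention acts on symptoms, and that it yields knowledge to act on. The same paragraph also describes the model as relating the trend in support to the trend in well-being.

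**The concern.** Two features of hypothesis 3 do not fit a causal reading.

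First, half of what is to be predicted is the seeker's level before the first letter. No support received on the platform can have produced it. A positive path to it would still count as support for the mechanism under the hypothesis as worded.

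Second, randomisation in this trial allocates seekers to Acceset or to the waiting list. Hypothesis 3 works inside arm 1 and relates each seeker to the befriender who chose that seeker. Anything that influences both the choice and the seeker's course can create an association, or hide one, whatever the support does. Optional discontinuation adds to this, because whether a befriender stays can depend on what the seeker writes.

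At stake is the conclusion of aim 3. The trial could report how peer support works when the data show only how pairs were formed. The arm comparison under hypothesis 2b is not affected.

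**Working it through.** **The plan's own figure.** The document gives 50 seekers per arm, a .05 significance level and 80% power, but no target effect. By the two-sided normal approximation, 50 per arm corresponds to d = (1.960 + 0.842) × √(2/50) = 0.56. This figure concerns the two-arm comparison. The article gives no figure for hypothesis 3, so there is none to reproduce.

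**Step 1: order in time (no assumption needed).**
- Predicted quantity: the seeker's growth factors, initial level included (Textbox 1).
- When that level is measured: before the intervention (Participants and Study Setting).
- When support reaches the seeker: in letters after that point.

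The support comes after the level. Apart from chance, a path between them must come from pairing or another non-causal link.

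**Step 2: is there room to choose?** 30 befrienders × 3 seekers = 90 places for 50 arm 1 seekers, or 50/30 = 1.67 seekers per befriender on average. There is.

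**Step 3: how often could pairing alone give a significant positive link?** The documents give no correlations, so these are assumptions:
- the true effect of support on the seeker is zero;
- pairing induces a correlation ρ between befriender support and seeker baseline;
- seeker baseline and slope correlate at 0.5;
- a simple correlation test at two-sided 5% stands in for the latent growth paths.

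Fisher z, n = 50, independence assumed: chance ≈ Φ(atanh(r) × √47 − 1.960), with √47 = 6.856.
- Level, r = 0.2: 0.2027 × 6.856 = 1.390, so Φ(−0.570) = 28%.
- Level, r = 0.3: 0.3095 × 6.856 = 2.122, so Φ(0.162) = 56%.
- Slope, r = 0.5 × 0.2 = 0.10: 0.1003 × 6.856 = 0.688, so Φ(−1.272) = 10%.
- Slope, r = 0.5 × 0.3 = 0.15: 0.1511 × 6.856 = 1.036, so Φ(−0.924) = 18%.

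A simulation with 50 seekers and 30 befrienders holding up to three places each (2000 runs per setting) lets seekers share a befriender:

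| Assumed ρ | Mean r, level | Significant and positive, level | Mean r, slope | Significant and positive, slope |
|---|---|---|---|---|
| −0.5 | −0.48 | 0% | −0.24 | 0% |
| 0 (random pairing) | 0.00 | 2.3% | 0.00 | 2.4% |
| 0.2 | 0.19 | 25% | 0.09 | 10% |
| 0.3 | 0.28 | 53% | 0.14 | 16% |
| 0.5 | 0.48 | 95% | 0.23 | 37% |

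The two methods agree closely. The simulated figures at 0.2 and 0.3 are equal or slightly lower, because the correlation achieved falls a little short of the target. Random pairing returns the nominal 2.5% upper tail.

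**Step 4: direction.** At ρ = −0.5 the induced correlations are negative. If befrienders who give stronger support take on harder cases, pairing would hide a real link.

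**Step 5: stated safeguards.** The article mentions no adjustment for how pairs were formed. The t tests in the analysis section compare completers with dropouts. The limitations name self-report and the single site.

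**The case against.** **The model may already be trend on trend.** One sentence of the analysis section describes it so, and the path diagram (Figure 3) is not available here. The Mechanism of Action section, which asks "whether and how the level at the start of the study and the rates of change" in befrienders' support relate to well-being, concerns the befriender's starting level as a predictor. This is fair, and the trend sentence is close to the remedy below. But the hypothesis itself, stated twice, includes the seeker's initial level, and it is the hypothesis that will be declared supported or not.

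**Selection on distress is not documented.** A reader might infer that befrienders pick easier seekers, so that the bias favours the hypothesis. The documents do not say so. Befrienders see the social context, not a distress score, timing and availability also matter, and screening excludes PHQ-9 above 9, which narrows the range on that scale. Handing on relates more directly to difficult content, but it is optional and depends on the befriender's discomfort. This objection stands: neither strength nor direction is known.

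**Hand-overs.** A reader might also infer that the model credits support to a befriender who has stopped writing. The article does not say how replaced befrienders are linked, and such a detail is commonly left to the analysis plan. It is not a finding.

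**The percentages are partly built in.** They assume a correlation and report the chance of detecting it. They are also not false-positive rates for hypothesis 3 as a whole, which names several paths. Both remarks are right, so the figures serve as illustration only.

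**Matching by choice is deliberate.** It is, and it can stay.

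**Conclusion.** The point holds for the criterion in hypothesis 3 and for its causal reading. That a path to the seeker's initial level is no evidence of mechanism follows from the order of measurement and needs no assumption. That the path to the rate of change is open to bias follows from pairing by choice within one arm, and the bias could go either way.

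The size depends on assumed values. With a selection correlation of 0.2 to 0.3 and no true effect, a significant positive link to level appears in about 25% to 55% of trials. With a further assumed baseline-slope correlation of 0.5, a link to slope appears in about 10% to 16%. The nominal rate is 2.5%. The slope figures matter more, since only that path could speak to mechanism.

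A covariate list in a fuller analysis plan could reduce the problem for the slope, but it could not turn the level path into evidence. The consequence is confined to aim 3.

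**What to change.** Leave the matching procedure as it is and change how hypothesis 3 is judged.

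1. Restrict the evidence for hypothesis 3 to the path to the seeker's rate of change, in line with the trend-on-trend sentence in the analysis section. A path to the seeker's initial level may be reported as a description of pairing.
2. Adjust the path to the rate of change for the seeker's baseline PHQ-9 and GAD-7 and for the social context selected before the first letter. All three are already collected. State that befrienders' lived experience, which the document names as a ground for choosing, remains unmeasured.
3. Add a sensitivity analysis that excludes or flags threads in which the befriender changed. Rebuilding support from the letters alone would not serve, since threads close after 21 days and letters cannot supply the baseline, week 6 and week 9 values that the growth curve needs.
4. Report the result as an association between support and seekers' change, not as a demonstrated mechanism, and list pairing by choice among the limitations.

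No new data are needed. The cost is that fewer paths can be claimed as support and that a few degrees of freedom are lost among 50 seekers.
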